### Comparators

2.5

Participants will be randomly assigned to the Bud App (intervention) or mental health fact sheets (control) group.

#### Intervention condition: Bud App

2.5.1

The Bud App is a self-guided digital intervention to support international students’ mental health and wellbeing. It targets modifiable risk factors, such as stress and social isolation, while strengthening protective factors, including social support and help-seeking behaviours. The app is intended for use across the continuum of psychological distress, from mild stress to heightened emotional states, but is not a crisis intervention tool. Instead, it provides timely, low-intensity support and directs users to crisis services when needed.

Bud was co-designed with international students to ensure that the app reflects the shared challenges and preferences of this population. While not formally adapted for specific cultural or linguistic groups due to the diversity within international student populations, Bud incorporates culturally sensitive design features, such as non-clinical framing (e.g., no use of terms like “diagnosis” or “therapy”), diverse student narratives, and peer-oriented content to reduce stigma and promote accessibility across a range of cultural backgrounds.

Bud's design is grounded in just-in-time adaptive intervention principles [25]. An emotion-tracking feature promotes emotional awareness and recommends contextually relevant coping tools. Core therapeutic content is based on ACT, CBT and DBT approaches, such as reframing cognitive distortions, using temperature-based distress tolerance techniques, practising gratitude, guided breathing techniques, and structured problem-solving [42,43]. The app also includes a brief suicide prevention gatekeeper course, designed to equip users with the skills to recognise and respond to signs of suicide risk in themselves and their peers, aligned with best-practice adaptations for non-Western contexts [30,31].

To normalise help-seeking and reduce mental health stigma, the app also features stories from international students who share their experiences of navigating mental health challenges and seeking support [44]. Lastly, a gamified element is included, where users earn points that contribute to the growth of their virtual ‘Bud’ character. Participants are free to engage with the app in a manner that suits their individual preferences, with optional daily mood check-in reminders through push notifications and flexible access to content.

#### Control condition: Mental health fact sheets

2.5.2

Participants assigned to the control group will receive access to four online psychoeducational fact sheets that provide general mental health information tailored for international students. These fact sheets were developed by a registered psychologist with experience in mental health communications and are representative of resources typically available on university websites and tertiary education platforms. The topics covered in the fact sheets include strategies for staying well through self-care, building and maintaining social connections, recognising the signs that indicate the need for mental health support, and information on how to access professional mental health services. Each fact sheet is designed to take approximately 5 min to read. All fact sheets will be available to participants, but they will be encouraged to read one fact sheet per week. Participants will receive weekly text reminders during the four-week study to access any fact sheets they haven't yet viewed. This flexible format lets participants engage with the content at their own pace and on their own schedule.

While this control condition was designed to reflect typical online supports provided to international students (e.g., psychoeducational materials), this represents a lower level of interactivity than the Bud app. This approach was selected to mirror “usual care” and to assess whether Bud offers additional benefit beyond the type of digital resources students commonly receive. A more technologically matched control could be considered in future research to isolate the effects of the intervention further. However, these options were beyond the current project's scope and resources.

### Recruitment

2.6

Participants will be recruited via digital communication channels serving international students, including student email lists, social media pages for international students in Australia, and institutional communication platforms, over 12 months. Partnerships with tertiary education institutions (e.g., University of Melbourne) and organisations (e.g. Study Melbourne) working with international students in Australia will facilitate recruitment. Recruitment materials will invite students to complete a brief online pre-screening survey hosted in REDCap, which includes eligibility questions confirming international student status (“Are you an international student currently studying at an Australian university?”), age (≥18 years), English language proficiency, and access to a smartphone (Android or iOS). Student status will therefore be verified through self-report, consistent with prior large-scale digital trials [19,20]. Interested students will access study information via a Participant Information and Consent Form (PICF) hosted on REDCap.

### Randomization

2.7

Participants will be randomly assigned to either the intervention or control group using a stratified block randomization approach with a block size of six. Stratification will be based on participants’ baseline suicidal ideation (SI) levels, as measured by the YSIS-3 [45], to ensure balanced allocation across three predefined strata: no or mild SI (scores 0–3), moderate SI (scores 4–6), and severe SI (scores 7 and above). The randomization sequence will be generated using a R and implemented within REDCap by a researcher independent of participant management, ensuring allocation concealment until assignment. Due to the nature of the intervention, participants cannot be blinded to their group allocation.

### Retention

2.8

Follow-up surveys will be emailed two weeks (T2) and four weeks (T3) post-baseline. To support retention, participants will receive up to three reminder emails for each follow-up survey. At each time point, participants will have a defined window to complete the survey (seven days for T2 and two weeks for T3). Participants will be compensated $15 for each completed survey via direct transfer, with payment details collected at baseline. All participants will be encouraged to complete follow-up surveys regardless of their engagement with the intervention or control materials to support an intention-to-treat analysis.

### Assessments

2.9

Assessments will be conducted remotely via REDCap (Research Electronic Data Capture [46,47]) at T1, T2, and T3 (see Table 2).A.*Descriptive Information.* Demographic variables collected at baseline (T1) will include age, gender, country of origin, time in Australia, nationality, education level, study area, degree level, self-rated English language proficiency, and current grade point average (GPA). In addition, participants will be asked to report on previous suicide attempts and considerations of attempts (past 12 months), self-harm behaviours (past 12 months), adjustment to university (College Adjustment Questionnaire: CAQ; [48]), and adverse childhood experiences (Adverse Childhood Experiences Checklist: ACEs [49]).B.*Outcomes.* Primary and secondary outcomes will be assessed at T1, T2 and T3.The primary outcome of this study is psychological distress measured with the Kessler Psychological Distress Scale (K10) [50]. This measure has been validated in diverse populations and is widely used in health related research [56]. Secondary outcomes will include key risk and protective factors for suicidal thoughts and behaviours targeted by the app, including help-seeking intentions using the General Help-Seeking Questionnaire (GHSQ [51]); Perceived burdensomeness and belonging using the Interpersonal Needs Questionnaire (INQ [52]); Emotion regulation using the Difficulties in Emotion Regulation Scale Short Form (DERS-SF [53]); Suicidal ideation using the Youth Suicide Ideation Screen–3 (YSIS-3 [57]); and mental health literacy with the Mental Health Learning Scale (MHL-9 [54]) adapted to refer to the interventions rather than school settings. All instruments are brief psychometrically validated tools designed for self-reporting and appropriate for digital intervention studies.C.*Acceptability and Iatrogenic effects.* Acceptability of the intervention will be assessed at T3 in the intervention group using the User Version of the Mobile Application Rating Scale (uMARS [55]) and a single general satisfaction item (e.g., how satisfied were you with the app?). To assess both acceptability and potential iatrogenic effects, participants in both trial arms will complete a custom measure previously used in suicide prevention research [58]. This measure captures perceived acceptability (e.g., whether the app or fact sheets were enjoyable or worthwhile) and potential iatrogenic effects (e.g., whether the content was upsetting or increased suicidal thoughts). Changes in suicidal ideation, along with monitoring of adverse events, will also provide additional insight into potential iatrogenic effects.D.*Engagement.* For the control intervention, the number of times the fact sheets are accessed will be recorded via REDCap. For the Bud intervention group, app usage data will be collected from participants to assess engagement and perceived usefulness of the Bud app. Specifically, this will include the total number of times the app is accessed, the number and type of activities completed, and responses to in-app prompts asking whether each activity was helpful. These metrics will quantify overall dosage and identify which features are most frequently accessed and perceived as most useful by participants. Participants will also have the opportunity to express interest in participating in an interview about their experience with the app.E.*Interview questions.* A subset of participants from the Bud intervention group who express interest will be randomly selected and invited to participate in online qualitative interviews conducted on Microsoft Teams. We will aim to recruit 20 participants. They will receive $30 for participating in an interview and will be asked to reflect on the app's design, usability, technical challenges encountered, and privacy and security concerns related to sharing personal information within the app. Additionally, the interview will explore the app's content regarding cultural appropriateness, relevance to their experiences as international students, their thoughts about how it could best be disseminated to international student populations, and suggestions for improvement.

**Table 2 tbl2:** Study measures at each time point.

Domain	Measure	# items	T1	T2	T3
Descriptive information	Demographic questionnaire	14	X		
	Previous Suicide attempts	2	X		
	Previous self-harm behaviours	1	X		
	Adjustment to University: CAQ [48]	14	X		
	Adverse Childhood Experiences: ACEs [49]	11	X		
Primary outcome	Psychological Distress: K10 (50)	10	X	X	X
Secondary outcomes	Help-Seeking: GHSQ [51]	12	X	X	X
	Perceived Burdensomeness: INQ [52]	5	X	X	X
	Sense of Belonging: INQ [52]	5	X	X	X
	Emotion Regulation: DERS – SF [53]	18	X	X	X
	Suicidal ideation: YSIS-3 (45)	3	X	X	X
	Mental health literacy: MHLS-9 (54)	9			X
Acceptability & iatrogenic effects	Open feedback question	1	X	X	X
	Acceptability and Iatrogenic effects: Custom Measure	6			X

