## Background

1

Suicide is a leading cause of death for young people aged 15–29 [1], and rates are particularly elevated in students enrolled in tertiary education, such as university or college [2]. International students comprise a significant proportion of tertiary education populations globally [3], yet they face unique challenges that can adversely affect their mental health [4]. Although past-year rates of suicidal ideation and self-harm are similar between international and domestic students (5.6–9.8 % vs. 5.2–13.3 % for ideation; 4.3–17.2 % vs. 3.2–22.9 % for self-harm), international students report higher rates of suicide attempts (1.21–2.2 % vs. 0.1–1.6 %) [5]. This elevated risk for severe outcomes appears to be driven by a complex interplay of stressors, including academic pressure, acculturative stress, and stigma [5].

Despite growing awareness of these risks, most suicide prevention still depends on traditional support, such as clinical treatment through health services or generic mental health information delivered universally by educational institutions [6]. There are two key limitations to these standard approaches. First, international students, including those who die by suicide, are less likely to engage with health services because of barriers such as stigma, visa concerns, low mental health literacy, and high treatment costs [[7], [8], [9], [10]]. Second, students who seek support often find services difficult to access when needed, poorly adapted to their cultural context, or mismatched to their expectations, leading to disengagement [11,12]. These findings highlight a clear need for suicide prevention strategies that are developed *with* and *for* international students and delivered in ways that are timely, relevant, and accessible [13].

Digital interventions targeting modifiable risk and protective factors for suicide represent a promising avenue for suicide prevention with international students [13,14]. They can offer scalable, low-cost, and on-demand support that overcomes key barriers to help-seeking and treatment utilization, particularly for culturally and linguistically diverse populations [14,15]. Evidence suggests that digital programs can improve mental health literacy, reduce stigma, enhance self-regulation skills, and, in some cases, directly reduce suicidal ideation [15,16].

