### Study sites

2.3

The study will be led by researchers at Orygen, the Centre for Youth Mental Health (CYMH) at the University of Melbourne. However, there are no specific study sites, as participants will be from a community sample and will access the interventions remotely using their mobile phones. Both interventions are designed to be used flexibly, allowing participants to engage at times and locations that are convenient for them. All study data will be collected through online surveys administered via REDCap.

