	***Intervention group only***				
	App usage (number and time accessing)	App metric		X	X
	Number and type of activities completed	App metric		X	X
	Perceive helpfulness of activities	In-app self-report		X	X
Total # of survey items per group			I = 96	I = 54	I = 92
			C = 96	C = 54	C = 69

Note: I = Intervention group, C = Control group. Each measure is described in detail below.

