### Safety management

2.11

A structured safety protocol is in place to monitor and respond to participant distress and suicide risk. Mental health support information, including crisis contacts and interpreter options, is provided multiple times, including in the app, on the control factsheets, survey completion screens, and PICF. At T1, T2, and T3, participants complete the Kessler Psychological Distress Scale (K10) and are asked if they are having thoughts of suicide (YSIS-3). At T2 and T3, they are additionally asked whether the app, factsheets, or surveys made them feel suicidal or want to self-harm. If a participant scores ≥30 on the K10, endorses suicidal ideation, or reports distress caused by study content, they are offered a wellbeing check-in and provided a list of relevant support resources they can contact. If they accept the check-in, a trained team member experienced in suicide risk assessments will review relevant data (e.g. suicidal ideation score from YSIS-3) and conduct a phone-based risk assessment within two business days. Suicide risk will be based on the phone assessment across four levels (none, low, moderate, high/life-threatening), and appropriate responses will be initiated, including emergency services if necessary (See Table 4). A study psychologist will be available to support staff conducting the risk assessments as required. Participants at life-threatening risk will be withdrawn from the study. Participants at other risk levels are reminded of support options and asked whether they wish to continue in the study.

**Table 4 tbl4:** Suicide risk levels and associated responses.

Risk Level	Definition	Action
None	No current suicidal thoughts or behaviour; participant reports no distress linked to study participation.	No action required beyond standard follow-up and support information.
Low	Passive thoughts of death or fleeting suicidal ideation without intent, plan, or significant distress.	Participant encouraged to access supports (e.g., helplines, psychologist) as required. Check whether they wish to continue in study.
Moderate	Suicidal ideation present with some associated distress, but no immediate plan or intent to act; participant can ensure their safety.	Participant encouraged to access supports (e.g., helplines, psychologist) as required. Check whether they wish to continue in study.

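### Suicide attempts and self-harm are not systematically asked about after baseline, so events can be missed in either arm and the safety conclusion under Aim 4 is weakly supported for suicidal behaviour

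*Protocol article*

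**What the plan says.** **Baseline.** Section 2.9, part A (Descriptive Information), states that "participants will be asked to report on previous suicide attempts and considerations of attempts (past 12 months), self-harm behaviours (past 12 months"). In Table 2 the row "Previous Suicide attempts" has two items and the row "Previous self-harm behaviours" has one. Both are marked at T1 only.

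**After randomisation.** Section 2.11 lists the K10 and the YSIS-3 at all three time points, and describes the YSIS-3 as a question about thoughts of suicide. It adds: "At T2 and T3, they are additionally asked whether the app, factsheets, or surveys made them feel suicidal or want to self-harm". Table 2 also has an open feedback item at every survey and a six-item custom acceptability and iatrogenic-effects measure at T3.

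**Other routes.** Section 2.9, part C, says: "Changes in suicidal ideation, along with monitoring of adverse events, will also provide additional insight into potential iatrogenic effects". Section 2.11 offers a wellbeing check-in when K10 is 30 or more, ideation is endorsed, or study content caused distress. A phone risk assessment follows if the participant accepts. Section 2.3 notes that "there are no specific study sites", and that all study data come from online surveys.

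**Purpose.** Aim 4 is to assess the app's safety. H9 predicts that no iatrogenic effects will be seen or reported in the Bud group, with increases in ideation or distress as its examples. The Background notes that "international students report higher rates of suicide attempts" than domestic students, while ideation and self-harm rates are similar.

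**The concern.** The trial tests a suicide prevention app, has no predefined exclusion criteria, and has a randomisation stratum for severe ideation. It asks about suicidal acts once, before allocation, and then uses the answers only as description. After that, the described questions cover thoughts, distress and urges linked to study material.

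Someone who self-harms in week 3, scores below 30 on the K10 at T3, endorses no ideation and does not attribute distress to the content meets no trigger. Unless that person volunteers the event, nothing described in the article would record it. The same holds for someone who meets a trigger but declines the check-in.

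The safety conclusion is what is at stake. H9 is confirmed by an absence of observations or reports, and such an absence says little about acts that participants were not asked about.

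**Working it through.** **1. Does the Table 2 schedule count any attempt or self-harm item after baseline?** The inputs are the item column and the time-point marks in Table 2. The stated figures are in the row "Total # of survey items per group": 96 at T1, 54 at T2, and 92 (intervention) or 69 (control) at T3.

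- T1: 14 + 2 + 1 + 14 + 11 + 10 + 12 + 5 + 5 + 18 + 3 + 1 = 96. This includes the 2 attempt items and the 1 self-harm item.
- T2: 10 + 12 + 5 + 5 + 18 + 3 + 1 = 54.
- T3 control: 54 + 9 + 6 = 69.
- T3 intervention: 69 + 2 + 20 + 1 = 92.

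All four totals reproduce exactly, so the three items are counted at T1 and nowhere else.

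**2. Is Table 2 complete for safety questions?** Not at T2. The 54 items are fully used by the K10, GHSQ, both INQ scales, DERS-SF, YSIS-3 and open feedback. Section 2.11 says a question about feeling suicidal or wanting to self-harm is asked at T2 as well as T3, but the custom measure is marked at T3 only. Table 2 and section 2.11 therefore disagree about T2. That question concerns feelings and urges, so the mismatch does not supply a question about acts.

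**3. How many events might occur?** The Background gives 1.21–2.2 % for attempts and 4.3–17.2 % for self-harm in international students. It attaches a past-year basis to ideation and self-harm; for attempts that basis is assumed here. It is also assumed that risk is even over the year and that these rates apply to this sample. Expected events = n × annual rate × 4/52, with n = 302:

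- Attempts: 302 × 0.0121 × 4/52 = 0.28, and 302 × 0.022 × 4/52 = 0.51.
- Self-harm: 302 × 0.043 × 4/52 = 1.0, and 302 × 0.172 × 4/52 = 4.0.

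A constant-hazard version, p = 1 − (1 − annual rate)^(4/52), gives 0.28–0.52 attempts and 1.02–4.35 people self-harming. The chance of at least one event in the trial, 1 − (1 − p)^302, is about 25–40 % for attempts and 64–99 % for self-harm. With the planned 20 % attrition (302 × 0.8 ≈ 242), the expected numbers are 0.23–0.41 and 0.82–3.49.

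**4. Could the arms be compared?** The constant-hazard four-week self-harm risks are 0.00338 and 0.01441. For a doubling of risk with 151 per arm, a two-sided 5 % comparison of two proportions has power of about 6 % at the lower risk and 14 % at the upper. The counts would be descriptive only.

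**The case against.** A reader might infer that the trial cannot detect suicidal behaviour at all after randomisation. The documents do not support that. Adverse event monitoring is stated. Both arms can be offered a check-in with a phone risk assessment by a trained team member, and the lowest risk level in Table 4 refers to behaviour as well as thoughts. The open feedback item could also reveal an event.

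Four further points stand in part:

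- **The full protocol is not shown.** It may say how adverse events are solicited and recorded, and an article commonly leaves that out. What remains is that the printed schedule places the behaviour items at baseline only.
- **The custom measure is described only by examples, and the YSIS-3 wording is not given.** It can be said that no described item asks about an act, but not that no item does. The mismatch at T2 also shows that Table 2 does not count every safety question, so the totals show what is counted rather than everything that is asked.
- **H9 names ideation and distress as its examples, and both are measured at all three time points.** No hypothesis names suicidal behaviour, and Bud is presented as an upstream programme. But the examples do not limit Aim 4, which is to assess safety.
- **Events will be few.** This is correct, and it is why only ascertainment is at issue.

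One might also infer that spontaneous reports would favour one arm because only app users are interviewed. That is speculative: about 20 people are sought, and the listed interview topics do not include safety events.

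**Conclusion.** The point holds as a gap in systematic ascertainment. On the schedule as printed, attempts and self-harm are asked about once, before allocation. Afterwards, detection depends on a monitoring process the article does not describe, or on a trigger followed by acceptance of a check-in. Participants who meet no trigger, decline the check-in or do not volunteer the event can be missed in either arm. A conclusion of no iatrogenic effects would therefore not be well supported for suicidal behaviour, although ideation and distress are covered.

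The expected numbers are small: about 0.3–0.5 attempts and 1–4 people self-harming among 302 over four weeks. They rest on the Background rates being annual (assumed for attempts), evenly spread and applicable to this sample. At least one case of self-harm is more likely than not across that range. The primary analysis is unaffected. The verdict would soften if the full protocol already solicits these events from every participant.

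**What to change.** - Repeat the three existing items at T2 and T3 in both arms, with the recall period changed to the time since the last survey.
- Report attempts and self-harm by arm as descriptive counts under Aim 4, with the number of participants who answered as the denominator and no between-arm test.
- State in section 2.11 that a positive answer enters the existing safety pathway. Which response it triggers is for the sponsor and the ethics committee to set.
- Reconcile Table 2 with section 2.11 on the safety question at T2, and correct the T2 total accordingly.
- If the full protocol already defines how adverse events are solicited from all participants, say so in section 2.9, part C.

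**Cost.** Three more items per follow-up survey: T2 goes from 54 to 57, T3 control from 69 to 72, and T3 intervention from 92 to 95. The T2 figure is before adding the section 2.11 question, whose item count is not given. The questions already exist in the baseline survey. The change needs an amendment that also touches the safety pathway, and may lead to a few more check-in offers.

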The selection of outcomes for this trial was guided by Bud's theory of change and its positioning as a community-level suicide prevention intervention. Designed to support international students across the continuum of psychological distress, Bud delivers evidence-based skills that address upstream risk and protective factors for suicide, offering early intervention for those not yet experiencing suicidal thoughts, and meaningful support for those who are. Accordingly, psychological distress was selected as the primary outcome due to its high prevalence in this population (with approximately 50 % reporting moderate to severe distress) [32,33], its robust association with suicidal thoughts and behaviours [34], and its demonstrated responsiveness to low-intensity self-guided digital interventions [35,36].

The secondary outcomes were selected to capture key suicide-related risk and protective factors targeted by the intervention. Help-seeking intentions were assessed due to consistent evidence that international students, including those who die by suicide, are often reluctant to engage with mental health services [8,9]. Perceived burdensomeness and sense of belonging were included based on their established associations with suicidality [37,38] and high relevance to international students, who frequently report experiences of academic underperformance, isolation, and cultural disconnection [4,5]. Suicidal ideation was included as a core suicide-related outcome to assess the app's impact on direct indicators of suicide risk. Mental health literacy was included because it supports symptom recognition, self-care, and help-seeking, and is often lower among international students compared to domestic peers [9,39]. Emotion regulation was included as a hypothesised mechanism of change, given its established link to reduced suicidal thoughts and behaviours [40]. This construct is targeted through several app features, including the emotion tracking and recommendation system, which aim to strengthen students' capacity to manage distress in the moment.

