	***Secondary outcomes***
	*H2:* Participants using Bud will report greater increases in help-seeking intentions compared to the control group at post-intervention.
	*H3:* Participants using *Bud* will report greater reductions in perceived burdensomeness and thwarted belongingness compared to the control group at post-intervention.
	*H4:* Participants using *Bud* will report greater improvements in emotion regulation compared to the control group at post-intervention.
	*H**5**:* Participants using *Bud* will report greater increases in mental health literacy from the intervention than the control group.
	*H6:* Participants using *Bud* will report greater reductions in suicidal ideation compared to the control group.
**Aim 2:** To assess the acceptability of the Bud app among international student users	*H7:* Participants in the Bud group will rate the app as acceptable, including positive evaluations of its engagement, functionality, aesthetics, information quality, and overall subjective quality.
**Aim 3:** To assess engagement with the Bud app	*H8:* Participants in the Bud group will demonstrate high engagement, reflected in app usage metrics and perceived helpfulness of activities.
**Aim 4:** To assess the safety of the Bud app	*H9:* No iatrogenic effects (e.g., increases in suicidal ideation or psychological distress) will be observed or reported among participants in the Bud group.

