#### Main analyses

2.10.2

Changes in the primary and secondary outcomes will be evaluated using generalised linear mixed models (GLMMs), including random intercepts for participants, random slopes for time, and fixed effects for group, time, and their interaction. For zero-inflated outcomes such as suicidal ideation (e.g., a large number of individuals reporting no ideation), model diagnostics will be used to assess the appropriateness of the GLMM approach, with consideration of alternative specifications (e.g., two-part models such as the zero-inflated Poisson model) if indicated [60,61]. Measures of acceptability and iatrogenic effects will be assessed with descriptive statistics. Pearson correlations will explore associations between app engagement and mental health outcomes. Exploratory analyses will investigate potential moderators, including demographics (e.g., gender and country of origin) and emotion regulation, for the primary and secondary outcomes, as well as for the engagement and acceptability measures. Sensitivity analyses will be conducted to assess whether outcome patterns differ as a function of intervention engagement or baseline stratification levels of suicidal ideation.

Interview data will be analyzed using a rapid qualitative coding analysis, drawing on principles of Framework Analysis [62,63]. This method is well-suited to small samples and time-sensitive evaluations, allowing for systematic and transparent interpretation of participant feedback across key domains [63]. A deductive coding framework will be developed based on the study aims (e.g., app acceptability, usability, engagement, and perceived impact), while remaining open to inductive insights raised by participants. Data will be summarised within NVivo to facilitate cross-case comparisons and identification of common themes and divergent experiences. This approach balances rigour and practicality and is commonly used in applied health and digital mental health research. Analysis will begin once all interviews are completed.

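### The mental health literacy outcome (H5) most plausibly records perceived learning from the assigned material, so it cannot support a claim that Bud improved literacy

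*Protocol article*

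**What the plan says.** The Abstract lists mental health literacy among the secondary outcomes. The Background gives the reason: "Mental health literacy was included because it supports symptom recognition, self-care, and help-seeking", and adds that international students often have less of it than domestic students. H5 in Table 1 predicts that Bud participants "will report greater increases in mental health literacy from the intervention than the control group".

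Section 2.9 names the instrument: "mental health literacy with the Mental Health Learning Scale (MHL-9 [54]) adapted to refer to the interventions rather than school settings". The next sentence states: "All instruments are brief psychometrically validated tools designed for self-reporting and appropriate for digital intervention studies". The same section says "Primary and secondary outcomes will be assessed at T1, T2 and T3", but Table 2 marks the literacy row at T3 only, with nine items. Section 2.10.2 plans one family of mixed models for the primary and secondary outcomes, with "random slopes for time, and fixed effects for group, time, and their interaction".

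Section 2.7 says that participants cannot be blinded. Section 2.5.2 describes the control material as four fact sheets, and accepts that they are less interactive than the app.

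**The concern.** The construct that is named and the construct that is probably measured differ. The Background treats literacy as something a student has, whatever its source. A learning scale reworded to refer to the interventions asks about something else, namely what the assigned material gave the participant. A student who was well informed at entry and learned little could score low. A student who liked the material but still knows little could score high.

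Randomisation does not remove the problem. It balances prior literacy between the arms in expectation, but the arms would still be answering about different objects, the app in one and the fact sheets in the other. Actual literacy could be equal at T3 while the scores differ.

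What is at stake is the published conclusion. Under the present label, a positive H5 would be reported as improved mental health literacy, and the trial holds no other measure against which to check that claim.

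**Working it through.** The check has two parts: whether a baseline exists, and what the score can be read as.

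**1. Is the T3-only mark in Table 2 real or a typesetting slip?** The item totals in Table 2 settle this.

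- Items repeated at every survey: K10 10 + GHSQ 12 + INQ burdensomeness 5 + INQ belonging 5 + DERS-SF 18 + YSIS-3 3 + open feedback 1 = 54.
- T1: 54 + demographics 14 + suicide attempts 2 + self-harm 1 + CAQ 14 + ACEs 11 = 96. Table 2 states 96.
- T2: 54. Table 2 states 54.
- T3, control: 54 + literacy scale 9 + custom measure 6 = 69. Table 2 states 69.
- T3, intervention: 69 + funder questions 2 + uMARS 20 + interview invitation 1 = 92. Table 2 states 92.

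All the totals reproduce with the scale at T3 only. Had it also been given at T1 and T2, the totals would be 96 + 9 = 105 and 54 + 9 = 63. The scale therefore has no baseline, and no within-person change can be calculated from it. Any increase has to come from how the items are worded.

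**2. What does the score record?** The items are not shown, so this is an inference. Four features of the document point the same way.

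- Section 2.9 calls the instrument a learning scale.
- Its wording has been changed to refer to the interventions.
- Of the six secondary-outcome rows in Table 2, it is the only one not given at all three time points. That fits items which make sense only after exposure.
- Among H2 to H6, only H5 attributes the gain to the intervention itself.

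**3. Setting the two side by side.**

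| | Outcome label and rationale | Score as collected |
|---|---|---|
| Object | the student's literacy | most plausibly, learning from the assigned material |
| Same object in both arms | yes | most plausibly not: app or fact sheets |
| Baseline | needed for change | none |
| Blinding | – | none |

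The score fits H5 if H5 is read as reported learning. It does not fit the label or the rationale.

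**4. Validation.** The sentence on validated tools covers all instruments and directly follows the statement that this one was adapted. Nothing in the document extends validation to the version with a new referent and setting. The abbreviation also differs: MHL-9 in the text, and "Mental health literacy: MHLS-9 (54") in Table 2.

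**The case against.** The strongest reply is that H5 already says what it should. It predicts what participants will report, and it ties the gain to the intervention. A scale that refers to the intervention and is given once afterwards can test that. This stands. A reader might infer that the instrument cannot support H5 at all, and the wording of H5 does not bear that out. The mismatch is with the outcome label and the Background rationale.

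A second reply is that no item, stem or response format is shown, so perceived learning is inferred, as is the use of different referents in the two arms. This also stands, and the point is worded accordingly. The Background, too, says what literacy supports; it does not define literacy as tested knowledge.

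Third, a reader might infer a bias towards Bud, because the control material amounts to about 4 × 5 = 20 minutes of reading while app use is unrestricted. The document does not establish this. It gives no exposure time for Bud, whose users may use it as little as they like. The fact sheets directly teach the signs of needing support and the routes to services, and control participants receive weekly reminders. Perceived learning could favour either arm. Open-label self-report also affects every other outcome in the trial; what is particular here is that the object being rated appears to change with the arm.

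Finally, the adaptation is disclosed next to the validation sentence, so that part is minor. It remains a sentence that claims more than the document supports.

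**Conclusion.** The point holds as a mismatch between label and measure. A T3 difference on this scale can address H5 as reported learning from the intervention. It cannot support a conclusion that Bud improved mental health literacy.

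The whole of the literacy conclusion is affected, because these nine items are the only literacy measure in Table 2. The direction and size of any bias cannot be derived from the document.

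The absence of a baseline and of blinding is documented. That the score reflects perceived learning, and that each arm rates its own material, is a strong inference from the scale's name, its adaptation, its timing and the wording of H5; sight of the adapted items would confirm or correct it. The primary outcome is not touched. The matter belongs in this document because the label, instrument and hypothesis are all fixed here, and no later modelling choice can turn a rating of material into a measure of literacy.

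**What to change.** - In section 2.9, Table 1 and Table 2, label the outcome *perceived mental health learning from the assigned material*, and use one abbreviation for the scale.
- Restate H5 as a between-group comparison of that score at T3: Bud participants will report greater perceived learning from the assigned material than control participants. Note that a single post-intervention score is not analysed with a group-by-time term.
- State that the score does not by itself support a claim about mental health literacy.
- Limit the sentence on psychometric validation so that it does not cover the adapted version.

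The outcome may remain secondary. The cost is wording only, with no added items and no change to the surveys. The downside is that the trial gives up a literacy claim.
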